#### Data Collection

Participants who provide informed written consent and agree to participate in the study will be asked to complete a baseline assessment questionnaire that captures both demographic and clinical information. At 6, 12, and 24 weeks, an online survey link will be sent to participants via email or text messages along with an invitation for them to complete the assessments. Participants will enter the email address or phone number through which they receive the messages as their study identifier at the start of the survey so that their data at the 4 time points can be matched. Participants who have not completed their follow-up assessments within 3 days of the due date will be contacted by a research coordinator and reminded to do so, or if they require assistance to complete the assessment, such assistance will be offered, including the option to complete the assessment over the telephone. In instances where such assistance is required, a blinded research assistant will be asked to read out the survey questions to the participant and record their responses.

#### Outcome Measures

The primary effectiveness outcome measures for the study will be the differences between mean scores on the following scales measured at baseline, 6, 12, and 24 weeks for the two study arms: the PHQ-9, WHO-5, and GAD-7.

The PHQ-9 scale will be used to provide depression symptom scores [35]. The PHQ-9 is a 9-item validated instrument (associated with a Cronbach alpha of .89) that is used to diagnose and measure the severity of depression in general medical and mental health settings. Each of the 9 questionnaire items is scored between 0 (not at all) to 3 (nearly every day). Higher scores on the scale indicate higher levels of depression. The PHQ-9 demonstrated good convergent validity with related constructs with an adequate internal consistency [45].

The WHO-5 will be used to measure patients’ quality of life [46]. The WHO-5 is a short 5-item questionnaire that measures the subjective well-being of the respondents. The scale has adequate validity as an outcome measure in clinical trials and as a generic scale for assessing well-being over time or between groups [47].

Secondary outcomes include changed mean scores on the GAD-7 scale [37] at baseline, 6, 12, and 24 weeks for the two study arms, as well as participant dropout rates and satisfaction rates at 12 and 24 weeks in the two arms. The GAD-7 is a validated 7-item questionnaire (associated with a Cronbach alpha of .92) that is used to assess the self-reported levels of anxiety in respondents in the 2 weeks prior to assessment. Each item on the scale is scored between 0 (not at all) to 4 (nearly every day). Higher scores on the scale indicate higher levels of anxiety.

#### Data Analyses

We will summarize the baseline demographic and clinical characteristics of participants in raw values and percentages and compare them between the two treatment arms using chi-square or Fisher exact tests and appropriate *t* tests. The primary and secondary outcome measures will be analyzed using descriptive and inferential statistical analysis. For the primary outcome measures, we will use analysis of covariance (ANCOVA) to assess the change in scores between the two treatment arms, with baseline PHQ-9 and WHO-5 scores as covariates; the treatment arm as the independent variable; and PHQ-9 and WHO-5 scores at 6, 12, and 24 months as respective dependent variables for each time point. Secondary quantitative outcome measures will be compared using chi-square or Fisher exact tests and appropriate *t* tests.

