## Methods

### Study Design

The STEM study design is a mixed methods, hybrid type II implementation-effectiveness trial. This design evaluates the effectiveness of an implementation strategy or intervention, while also evaluating the implementation context associated with the intervention [38,39]. This study is a randomized noninferiority trial testing the outcomes for email messaging (as a strategy for delivering daily evidence-based supportive messages to patients with MDD in addition to usual care), in comparison to outcomes for text messaging, which has been deemed effective by previous studies (with noted implementation limitations [28,33]). The relevant guidelines and checklist were obtained from the Enhancing the Quality and Transparency of Health Research (EQUATOR) network website and used in the design of this trial [40]. These include the SPIRIT (Standard Protocol Items: Recommendations for Interventional Trials) checklist (Multimedia Appendix 1) and CONSORT (Consolidated Standards of Reporting Trials) guidelines (Multimedia Appendix 2) [41,42].

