### Sample Size

Based on the effect sizes (Cohen *d* of 0.85 and 0.67) achieved in 2 previous randomized trials (n<80 for each trial), which compared daily supportive text messages plus treatment as usual with treatment as usual alone for the management of patients with MDD, a sample size of 80 is estimated to have sufficient power for the current protocol. Allowing for a projected maximal 20% overall dropout rate, we propose to recruit 100 patients with MDD into the trial, with 50 patients randomly allocated into each study arm.

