### Effectiveness Evaluation

#### Hypothesis

As the same messages will be delivered through the supportive text message program and the email program, we hypothesize that daily email messaging will not be inferior to daily supportive text messaging in reducing depression symptoms and improving quality of life for patients with MDD. We further hypothesize that participant dropout rates and satisfaction rates will be comparable in the two arms of the study.

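### A declared noninferiority trial has no margin or confidence-bound rule in its primary ANCOVA and is sized on superiority effects, so it has almost no valid route to its main conclusion

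*Protocol article*

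**What the plan says.** Under Study Design, the protocol article states: "This study is a randomized noninferiority trial testing the outcomes for email messaging". Under Hypothesis it adds that "we hypothesize that daily email messaging will not be inferior to daily supportive text messaging in reducing depression symptoms", and extends this to quality of life. The same section expects that "participant dropout rates and satisfaction rates will be comparable in the two arms of the study".

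Under Data Analyses, for the primary outcomes, "we will use analysis of covariance (ANCOVA) to assess the change in scores between the two treatment arms". Baseline PHQ-9 and WHO-5 scores are the covariates, arm is the independent variable, and each follow-up time point has its own model. For the rest: "Secondary quantitative outcome measures will be compared using chi-square or Fisher exact tests and appropriate *t* tests".

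Under Sample Size, the number is justified as follows: "Based on the effect sizes (Cohen *d* of 0.85 and 0.67) achieved in 2 previous randomized trials". Those trials compared text messaging plus usual treatment with usual treatment alone. From them, "a sample size of 80 is estimated to have sufficient power for the current protocol", and 20% dropout raises this to 100, with 50 per arm. Alpha, sidedness, power and margin are not given.

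**The concern.** A noninferiority claim needs a statement of how much worse the new strategy may be and a rule that the data exclude a loss of that size. The article has neither. It pairs a no-worse hypothesis with a comparison of the two arms, and it takes its sample size from a different question: whether text messaging beats usual care.

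Without a margin, a comparison of arms can end in three ways. Email is significantly worse, which refutes the hypothesis. Email is significantly better, which supports it. Or there is no significant difference, which settles nothing. If the two strategies really are similar, as the article expects, the third result is by far the most likely, and the plan has no valid way to interpret it. Anyone who took it as support would be using a criterion that becomes easier to meet as patients are lost or measurements get noisier.

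This is the main effectiveness conclusion. The article's Conclusion and Discussion say the findings may inform policy and resource allocation and a planned multicenter trial.

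**Working it through.** **Inputs from the article.** 80 evaluable patients (40 per arm), 100 recruited, 20% dropout, d = 0.85 and 0.67 (Sample Size).

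**Assumptions, because the article gives no figure.** Two-sided 5% test (equivalently, one-sided 2.5% for noninferiority); baseline-to-follow-up correlation r of 0, 0.5 or 0.7; illustrative losses of 0.335 SD (half of 0.67) and 0.5 SD. SD is that of the follow-up score, and ANCOVA multiplies it by √(1 − r²).

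**1. The stated sample size.**
- 80 / (1 − 0.20) = 100, which matches.
- The 80 has no stated alpha or power. A two-sided 5% superiority calculation, n per arm = 2(1.96 + z_power)² / d², at d = 0.67 gives 35 per arm (70 in total) for 80% power and 41 per arm (82) for 85%. At d = 0.85 it gives 22 per arm (44) for 80% power. So 80 is consistent with a superiority calculation on d = 0.67 at about 85% power, and no margin enters it.

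**2. Precision.** SE of the arm difference = √(1 − r²) × √(2/40), that is 0.224, 0.194 and 0.160 SD for r = 0, 0.5 and 0.7. The 95% CI half-width (1.96 × SE) is about 0.44, 0.38 and 0.31 SD. At r = 0 and r = 0.5 it exceeds half of the 0.67 benefit.

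**3. Chance of a non-significant result when email is truly worse.** This is one minus the power of a two-sided 5% t test on 78 degrees of freedom, with noncentrality = loss / SE.

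| True loss with email | r = 0 | r = 0.5 | r = 0.7 |
|---|---|---|---|
| 0.335 SD | 68% | 60% | 46% |
| 0.5 SD | 40% | 28% | 13% |
| 0.67 SD (whole smaller benefit) | 16% | 7% | 1% |

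At r = 0 and 0.335 SD, for example, noncentrality = 0.335 / 0.2236 = 1.50. A margin-based test would hold the risk of wrongly declaring noninferiority at 2.5% when the true loss equals the margin.

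**4. What 80 evaluable patients give under a margin rule.** With a true difference of zero, power = Φ(margin / SE − 1.96). Total N for 80% power is twice 2(1 − r²)(1.96 + 0.84)² / margin², rounded up per arm.

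| Margin | Power with 80, r = 0 / 0.5 / 0.7 | Evaluable total for 80% power |
|---|---|---|
| 0.335 SD | 32% / 41% / 56% | 280 / 210 / 144 |
| 0.5 SD | 61% / 73% / 88% | 126 / 96 / 66 |
| 0.67 SD | 85% / 93% / 99% | 70 / 54 / 36 |

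With no gain from the covariate, 80 is adequate only if the margin is close to the whole 0.67 effect.

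**5. Dropout.** Near 20% with 50 per arm, the 95% CI half-width for the difference is 1.96 × √(2 × 0.2 × 0.8 / 50) = 0.157, about ±16 percentage points.

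**The case against.** Several objections have force.

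- **The article never says a non-significant result will be read as noninferior.** A reader might infer this because little else is on offer, but nothing is written about interpretation. The text supports only that a valid criterion is absent.
- **ANCOVA is not the wrong model.** A reader might conclude that the analysis must be replaced. It need not be: the adjusted difference and its confidence interval are what a noninferiority comparison uses. What is missing is the margin and the rule.
- **Direction is given.** Hypothesis says which strategy must not be worse, and Outcome Measures says higher PHQ-9 scores mean more depression. A significant result in favour of email would also support the hypothesis.
- **A journal article may leave a decision rule to a fuller protocol or analysis plan.** Sidedness and reporting detail could fairly be left there. A margin is different, because it should determine the sample size. The article does give its sample-size basis, and that basis is superiority effects from another comparison. This is a mismatch within the stated design.
- **The figures depend on assumptions.** Alpha, sidedness and correlation are not in the article. At r = 0.7 the chance of missing a 0.335 SD loss falls to 46%, and a loss of the whole 0.67 SD would seldom be missed. The size of the problem varies; its existence does not.
- **Dropout and satisfaction are secondary, with a loose expectation of similarity.** That part is a minor reporting matter.

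**Conclusion.** The point holds and should be fixed before the arms are compared. Design and hypothesis are noninferiority, while the stated primary analysis has no noninferiority criterion and the sample size has no margin. Unless email proves significantly better, the plan as written cannot validly support its main conclusion.

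With 40 evaluable per arm and a two-sided 5% test, a loss of half the smaller cited benefit would go undetected in roughly half to two thirds of trials (46% to 68%), and a 0.5 SD loss in 13% to 40%. These ranges rest on assumed correlations of 0 to 0.7 and on losses chosen for illustration.

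**What to change.** Keep the ANCOVA and the data collection, and add the following to the protocol or analysis plan:

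1. Name one primary scale, PHQ-9, and one primary week. The article currently lists several primary scales at several time points.
2. Fix and justify a noninferiority margin before unblinding. The effects quoted in the Introduction are on the BDI-II, so a PHQ-9 margin cannot be read from them directly. State it in SD units, or in PHQ-9 points with the conversion shown as an assumption.
3. Conclude noninferiority only if the upper limit of the two-sided 95% CI for the adjusted difference (email minus text) is below the margin.
4. State that p > .05 is not evidence of noninferiority.
5. Replace the claim of sufficient power with the power that 80 evaluable patients give at the chosen margin: about 32% to 56% at 0.335 SD.
6. As a minor addition, report dropout and satisfaction as differences with 95% CIs.

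The change needs no new data and no new model. The cost is that the trial may have to report an inconclusive result. At a margin of 0.335 SD, 80% power would need 144 to 280 evaluable patients, so the sponsor would have to either accept low power openly or revisit the sample size.

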### Study Aims and Objectives

The *Supportive Text vs Email Messaging* (STEM) trial aims to evaluate comparatively the implementation and impact of two implementation strategies (text messaging and email messaging) for delivering supportive messages to patients with MDD.

The specific objectives are outlined below:

Implementation evaluation:To compare the impact of both strategies for delivering the daily supportive messages on implementation outcomes (adoption, fidelity, reach, cost, sustainability);To evaluate contextual factors that could inhibit or facilitate the implementation of each strategy.Clinical effectiveness evaluation:To compare the mean difference in Patient Health Questionnaire-9 (PHQ-9) [35] scores from baseline and at 6, 12, and 24 weeks for patients with MDD receiving standard care plus daily supportive email messages to those receiving standard care plus daily supportive text messages;To compare the quality of life using the 5-item World Health Organization Well-Being Index (WHO-5) [36] at baseline and at 6, 12, and 24 weeks for patients with MDD receiving standard care plus daily supportive email messages to those receiving standard care plus daily supportive text messages;To compare anxiety levels using the Generalized Anxiety Disorder-7 (GAD-7) scale [37], at baseline and at 6, 12, and 24 weeks, as well as the dropout and satisfaction rates between patients in the two treatment arms.

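### GAD-7 is listed as both primary and secondary, and under neither label does it get the baseline-adjusted analysis planned for PHQ-9 and WHO-5

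*Protocol article*

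**What the plan says.** **Status of GAD-7.** Outcome Measures opens by defining the primary effectiveness outcomes as differences in mean scores on three scales "measured at baseline, 6, 12, and 24 weeks for the two study arms: the PHQ-9, WHO-5, and GAD-7". Later the same section states: "Secondary outcomes include changed mean scores on the GAD-7 scale", followed by dropout and satisfaction rates.

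**Baseline.** Study Aims and Objectives has anxiety compared on GAD-7 "at baseline and at 6, 12, and 24 weeks, as well as the dropout and satisfaction rates between patients in the two treatment arms". A baseline score is therefore collected.

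**Analysis.** For the primary measures, Data Analyses specifies ANCOVA "with baseline PHQ-9 and WHO-5 scores as covariates; the treatment arm as the independent variable", with PHQ-9 and WHO-5 at each follow-up as the dependent variables. GAD-7 appears neither as covariate nor as dependent variable. The section then says: "Secondary quantitative outcome measures will be compared using chi-square or Fisher exact tests", and the sentence ends by adding t tests, described only as appropriate.

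**Item scoring.** For GAD-7, Outcome Measures says: "Each item on the scale is scored between 0 (not at all) to 4 (nearly every day"). For PHQ-9 it says: "Each of the 9 questionnaire items is scored between 0 (not at all) to 3 (nearly every day").

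**The concern.** Of the secondary outcomes listed in Outcome Measures, GAD-7 is the only continuous scale, so the t test in the secondary-outcome sentence falls to it. If GAD-7 is instead primary, the ANCOVA sentence ought to cover it, but the model as written has no place for it. Either way, an outcome with a recorded baseline is left without the model chosen for the other two scales.

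Two things are at stake. One is precision: the anxiety comparison would have a wider confidence interval than the same data could give. The other is chance imbalance. A follow-up-score comparison leaves a baseline difference between arms uncorrected, and a change-score comparison over-corrects it. Both matter in a trial of this size, where anxiety is a stated comparison and a wide, non-significant result could be misread as showing no difference.

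**Working it through.** **Inputs.** Sample Size gives 80 evaluable patients and 20% dropout. The recruitment figure reproduces: 80 / (1 − 0.20) = 100, or 50 per arm. With 1:1 allocation, 80 evaluable is 40 per arm. The baseline to follow-up correlation r for GAD-7 is not given, so 0.3, 0.5 and 0.7 are assumed. SDs are assumed equal at baseline and follow-up.

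**Formulas.** The large-sample variance of the between-arm difference, with a follow-up-score t test set to 1, is:

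- change-score t test: 2(1 − r)
- ANCOVA: 1 − r²
- ANCOVA relative to change score: (1 − r²) / [2(1 − r)] = (1 + r)/2

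Both ANCOVA ratios are below 1 for any r between 0 and 1.

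| r (assumed) | Change score | ANCOVA | ANCOVA vs follow-up | ANCOVA vs change |
|---|---|---|---|---|
| 0.3 | 1.40 | 0.91 | 9% lower | 35% lower |
| 0.5 | 1.00 | 0.75 | 25% lower | 25% lower |
| 0.7 | 0.60 | 0.51 | 49% lower | 15% lower |

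**Interval width.** With 40 per arm, the 95% half-width for a follow-up-score t test is 1.96 × √(2/40) = 0.438 SD. Multiplying by the square root of each variance gives:

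- ANCOVA: 0.418, 0.380 and 0.313 SD at r = 0.3, 0.5 and 0.7
- change-score t test: 0.519, 0.438 and 0.339 SD

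**Equivalent sample size.** To match ANCOVA on 80 patients:

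- a follow-up-score t test needs 80 / (1 − r²), about 88, 107 and 157
- a change-score t test needs 80 × 2 / (1 + r), about 123, 107 and 94

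**Chance imbalance.** The standard error of a baseline mean difference is √(2/40) = 0.224 SD. A gap of at least 0.3 SD in either direction has z = 0.3 / 0.224 = 1.34, a probability of about 18%. At r = 0.5, a 0.3 SD gap shifts a follow-up-score comparison by r × 0.3 = 0.15 SD, and a change-score comparison by (1 − r) × 0.3 = 0.15 SD in the opposite direction. ANCOVA removes the shift.

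**Item range, separately.** Seven items scored 0 to 4 give a maximum of 7 × 4 = 28. Scored 0 to 3, the maximum would be 7 × 3 = 21. The article states no GAD-7 total against which to check this.

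**The case against.** The strongest reply is that a t test between randomised arms is a valid analysis and that anxiety is peripheral. It appears in none of the hypotheses and does not drive the sample size. That is right, and it limits the point to efficiency.

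Second, the reference to changed mean scores suggests a change-score test, which does use the baseline. A reader might infer that the plan ignores baseline GAD-7 altogether, but the text does not support that. The form of the t test is left open, and the calculation therefore covers both. ANCOVA is more precise than either.

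Third, if GAD-7 is primary, the opening of the ANCOVA sentence could be said to include it. The sentence then lists its covariates and dependent variables, however, and GAD-7 is absent, so that reading does not supply a model.

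Fourth, a reader might infer that a t test would make the anxiety result incomparable with the PHQ-9 and WHO-5 results. That does not follow: under randomisation both t tests and ANCOVA estimate the same between-arm mean difference for a scale. Only precision and the handling of chance imbalance differ.

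Fifth, the item ranges of two different instruments need not agree. The shared end anchors hint at a slip but are not a contradiction, and the article states only 0 to 4 for GAD-7.

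**Conclusion.** The point holds as a conflict over the status of GAD-7 together with an avoidable loss of precision. The stated method is inconsistent with the one chosen for PHQ-9 and WHO-5, and this is a written choice, not a detail left to another document. It does not make the anxiety analysis biased or invalid.

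The size depends on an unstated correlation. Over r from 0.3 to 0.7, ANCOVA lowers the variance by 9% to 49% against a follow-up-score t test and by 35% down to 15% against a change-score t test. It would be tempting to say that the plan costs the equivalent of a third more patients, but that is the single value r = 0.5 (1 / 0.75 = 1.33). The figures rest on equal SDs, 80 evaluable patients and large-sample formulas; estimating the slope costs one of 78 degrees of freedom.

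The item range is a separate minor query and adds no weight to this conclusion.

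**What to change.** - In Outcome Measures, state once whether GAD-7 is primary or secondary, and make the two statements agree.
- In Data Analyses, add GAD-7 under whichever label stands: the same ANCOVA as for PHQ-9 and WHO-5, at 6, 12 and 24 weeks, with baseline GAD-7 as covariate. Data Analyses currently gives these time points in months where the other sections give weeks, so the unit should be aligned in the same edit.
- Keep chi-square or Fisher exact tests for dropout and satisfaction rates.
- Separately, confirm the 0 to 4 GAD-7 item range against the instrument before totals are computed.

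The cost is a sentence or two of text. Baseline GAD-7 is already collected, and no change in sample size or visits is needed.

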### Implementation Evaluation

Implementation evaluation will seek to explore and compare the context, process, and outcomes of implementing the two strategies, guided by the CFIR and the RE-AIM frameworks. A mixed method approach will be applied in evaluating the implementation of the STEM trial.

#### Data Collection

Quantitative data will be collected on the implementation outcomes: acceptability, fidelity (adherence to reading messages), and sustainability (continued utilization). Data will be collected using user satisfaction survey questionnaires at 6, 12, and 24 weeks for the two study arms.

Qualitative data will be collected via focus group (see details below) discussions involving the patients. The discussion topic guide will be informed by the CFIR domains and will also elicit participants’ views on barriers and facilitators to the implementation of both strategies.

We will invite a random sample of 10 participants via text message and email to take part in a virtual focus group workshop using end-to-end encrypted teleconferencing (with appropriate consent for confidentiality) to discuss the impacts of the interventions. In order to explore the reasons why participants remain or drop out of the study, we will hold a focus group for a cross-section of participants who remained in the study and those who dropped out to discuss the impacts of the supportive email and text message interventions. Thus, an invitation will go to both those who remain in the study and those who dropped out, and participation in the focus group workshop will be voluntary. We will offer a CAD $50 (US $39) gift card as honorarium to cover the cost for participants attending the focus group.

